### Randomized controlled trial

#### Study design

The experimental component of the mixed methods RCT will follow a 6-month 2-group parallel superiority design, with a 12–18-month observational follow-up (see Fig. 2 for details). There will be a 2:1 allocation of participants to the intervention versus the control group. The control group will consist of 6 months of standard care that adults can access in the Canadian Province of Manitoba, including any services and programs that are offered at NorWest, except Hans Kai. At the end of the 6-month control period, the control group participants will be offered the opportunity to join Hans Kai and, once in the intervention, they will be followed for up to 18 months. The participants in the intervention group will be followed for a minimum of 6 months (RCT period) and up to 18 months; however, the randomized controlled portion of the study will last for the first 6 months, while the observational follow-up for them will last 12 months. After baseline, there will be a 2-month period of Hans Kai program implementation during which program participants will attend the Hans Kai Health School, prior to starting regular group meetings.

**Fig. 2 Fig2:**
[figure not shown]
Hans Kai RCT design

During the 6-month RCT, the participants who are randomly assigned to the intervention group will complete four visits, while the participants who are randomly assigned to the control group will complete three visits (see Supplementary Table 1 for the SPIRIT flow diagram). Following the intervention period (6 months), during the follow-up observational study, both groups will complete two visits 6 months apart. There will be no formal screening period as only participants who are eligible to enter the Hans Kai program will be invited to participate in the RCT.

#### Study setting

The study will be conducted primarily at NorWest, which is a multidisciplinary health clinic located in the city of Winnipeg (Manitoba, Canada) that engages the community in a variety of co-operative health-based initiatives. NorWest delivers community-based services and programs including primary healthcare, community development, counselling, support services, early learning, and childcare. Eligible individuals throughout Winnipeg can access services in the areas of family violence, immigrant and refugee services, substance abuse during pregnancy, nursing foot care, and Indigenous health. Hans Kai is an ongoing program offered at NorWest. Additional sites in the city of Winnipeg, including any Winnipeg Regional Health Authority (WRHA) site, will also be added as needed to reach the desired sample size of 105 participants (see next section for details). Based on a previous evaluation of Hans Kai [18], it is expected that approximately 85% of the trial participants (*n* = 90) will attend the Hans Kai program and complete the assessment visits at NorWest (15% dropout rate).

#### Recruitment

For the purposes of this trial, study participants will be recruited in the city of Winnipeg using multiple strategies. A short script describing the opportunity to participate in the Hans Kai trial was developed in a collaborative effort between the study team and the program staff. The script will be used to develop ad hoc products (e.g., posters, flyers, ads, and PowerPoint presentation slides) to advertise the study on social media (including, Facebook and Instagram), via postering, on local radio and television channels, via media releases, and by presenting this opportunity to different groups. Posters will be placed in multiple locations across the city of Winnipeg, including community health centers and resource centers, schools, churches, and cultural centers. Additional posting sites may be added as needed. Additionally, using a slideshow, the opportunity to join the Hans Kai trial will be presented to groups that may be interested in participating, such as seniors, mothers of young children, and groups supported by community centers in the city of Winnipeg, which will be approached at the sites.

#### Participants

Participants may enter the trial if all the following apply: (i) age 18 years or older; (ii) any gender; (iii) willingness and ability to give informed consent for participation in the trial; (iv) ability to speak and read English at a grade 6 level; (v) self-reported motivation to making lifestyle changes that can positively impact someone’s health; (vi) stable health status that allow participating in the program activities, including performing light exercise (as determined by the participant and Hans Kai staff); and (vii) ability and willingness to comply with all trial requirements (as determined by the research team). Participants may not enter the trial if any of the following apply: (i) age under 18 years; (ii) cognitive impairment that prevents the person from providing informed consent or participating in the program activities (as determined by the study staff); (iii) existing relationship with the research team, such as supervisory or familial relationship; (iv) frailty that prevents the person from participating in group activities or exercise (as determined by a healthcare professional); (v) participation in another research trial in the past 12 weeks; (vi) instable health or serious illness, such as, dementia or a terminal illness, or recent significant medical diagnosis; and (vii) inability to comply with all trial requirements.

A research team member with extensive experience in conducting mixed methods research will screen potential participants, enrol eligible participants in the trial, and collect written informed consent from all trial participants. If required, following appropriate training, research assistants will also be involved in this process to support the research team.

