### The Hans Kai Program

The concept of Hans Kai or “group learning” originated in Japan, where this approach is used to help people enhance their health knowledge, their ability to monitor their own basic health indicators, and their wellness-focused behaviors [19]. Hans Kai was adapted to the Canadian context and healthcare system by a group of NorWest Co-op Community Health (NorWest; http://norwestcoop.ca) staff members who developed the Hans Kai program through collaborative efforts between healthcare professionals, community members, researchers and representative of the local government, and started offering it in 2010 [18].

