Hans Kai is a peer-led, preventative, self-sustaining, community-based health promotion program for adults with or without noncommunicable diseases who wish to maintain or improve their health. Hans Kai empowers individuals to take control of their own health and provides a unique opportunity for participants to have an active role in improving or maintaining their health and wellbeing. The program is a health promotion program for adults of all ages, genders, and socioeconomic circumstances that combines health education with social support in a peer-led, self-sustaining model.

Several features of this program distinguish it from other health promotion programs that are currently offered to Canadian adults, including the theoretical model behind it and its structure and content. Hans Kai is grounded in a holistic model of wellness [20] in which several social determinants of health at multiple levels of human ecology simultaneously interact to determine someone’s health status and overall wellbeing (see Fig. 1 for details). In line with this model, the program focuses on modifiable risk factors for poor physical health (e.g., diet, physical activity, noncommunicable diseases, access to health care services, and preventive care), as well as sleep, stress management, mental health, loneliness, and social support/connections.

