#### Intervention

In this trial, there will be two groups, an intervention group (*n* = 70) that will immediately enrol in the Hans Kai program and a control group (*n* = 35) that will access standard care available in the Canadian Province of Manitoba, including any services and programs offered at NorWest, except Hans Kai. There will be no special criteria for discontinuing or modifying allocated interventions, except in cases involving worsening of pre-existing health conditions that may either put participants at risk if they continue the program or hinder their participation in the program. The program that will be the intervention in this trial is the Hans Kai program offered at NorWest, with the only modifications being the trial assessment visits described below. The minimum level of compliance to the intervention is 80%; to remain in the trial, study participants must attend a minimum of six health school sessions.

Participants in the control group will remain as close to a “typical” community member as possible as they will be able to receive any other health programming normally available to them in Winnipeg, except the Hans Kai program. Standard of care will be made available to all members of the control group in compliance with the healthcare rights of Canadians and Manitobans holding a Manitoba health card. NorWest staff will provide support to the community members without a Manitoba health cards in obtaining one. The only deviation from standard care in the control group will be the baseline, 3-month, and 6-month visits described below during which the control participants will complete questionnaires and undergo physical assessments.

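### The eligibility list does not keep out past Hans Kai participants, although the program has run since 2010 and continues at the main trial site

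*Protocol article*

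**What the plan says.** The Participants section gives seven inclusion and seven exclusion criteria. The exclusions are introduced by "Participants may not enter the trial if any of the following apply". The only one about previous participation in anything is "participation in another research trial in the past 12 weeks", which concerns research studies and not the program.

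The Hans Kai Program section says that NorWest staff adapted the program "and started offering it in 2010". Study setting names NorWest as the main site and adds that "Hans Kai is an ongoing program offered at NorWest".

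Three other places bear on who may enter:

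- Study design, in the text after Fig. 2, says that "only participants who are eligible to enter the Hans Kai program will be invited to participate in the RCT".
- The last inclusion and the last exclusion criterion (both numbered vii) require that a participant can comply with all trial requirements.
- The Intervention section lets controls use "any other health programming normally available to them in Winnipeg, except the Hans Kai program".

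The program itself is described broadly: "The program is a health promotion program for adults of all ages, genders, and socioeconomic circumstances". No section makes never having attended a condition of joining it.

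**The concern.** The trial is meant to compare starting Hans Kai with not having it. A person who completed the health school some years ago, or who belonged to a group and then stopped, passes every listed criterion and can be randomized.

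Three things are at stake:

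- **Intervention arm.** Someone repeating the program may gain less from it than a newcomer, which lowers the arm's mean change.
- **Control arm.** After the health school, groups choose their own times and places and meet independently of facilitators. A control with ties to such a group could go on attending it, and the staff's withholding of new enrollment would not by itself prevent that.
- **Secondary analysis.** Statistical analysis plans a test involving the length of time spent in the program, from 0 to 20 months. For a past member, trial entry is not time zero, so this variable is misclassified.

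The trial plans for about 80% power with 90 evaluable participants, so it has little reserve against dilution.

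**Working it through.** **1. Does any text bar past participants?**

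| Text | Current member | Past graduate or lapsed member |
|---|---|---|
| Exclusion (v), other research trials, 12 weeks | Not covered | Not covered |
| Eligible to enter the program (Study design) | Perhaps covered | Not covered |
| Compliance items (vii) with six control months without Hans Kai | Probably covered if the person means to keep attending | Not covered |

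The gap that remains is past graduates and lapsed members. Such people exist: the Background reports an earlier evaluation of the program with 63 adults. How many would volunteer for the trial is not stated.

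**2. Reproduce the plan's own figures.** Inputs from Sample size: SD of change 5, 60 intervention and 30 control participants, 80% power, detectable difference 3.1. From Statistical analysis: significance level 0.05, taken as two-sided because the difference is given with both signs.

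- Standard error = 5 × √(1/60 + 1/30) = 1.118.
- Power for 3.1 = Φ(3.1/1.118 − 1.96) = Φ(0.81) = 79.2% (78.3% with the t distribution).
- Difference for exactly 80% power: 3.13 (normal) or 3.17 (t).
- Ten groups against 30 controls: 5.11 (normal) or 5.25 (t), against the stated 5.2.

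The stated figures hold.

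**3. Add prior exposure.** Let f be the share of randomized people already exposed, equal in both arms in expectation, and k the fraction of the newcomer effect that they still show. The mean contrast is then 3.1 × [1 − f(1 − k)]. Neither f nor k is in the documents, so both are assumptions. The SD is held at 5.

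| f | Contrast, k = 0 | Power, k = 0 | Evaluable N for 80%, k = 0 | Contrast, k = 0.5 | Power, k = 0.5 |
|---|---|---|---|---|---|
| 0 | 3.10 | 79.2% | 93 | 3.10 | 79.2% |
| 5% | 2.945 | 75.0% | 102 | 3.02 | 77.1% |
| 10% | 2.79 | 70.4% | 114 | 2.945 | 75.0% |
| 20% | 2.48 | 60.2% | 144 | 2.79 | 70.4% |

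Power is Φ(contrast/1.118 − 1.96). The N column is three times the control-arm size, which is (1.96 + 0.84)² × 25 × 1.5 / contrast², rounded up.

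In the scenario with groups as units (10 against 30, t distribution, k = 0), power for 5.2 goes from 79.3% to 70.5% at 10% exposed and 60.3% at 20%.

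**The case against.** The strongest reply is that much of this is already covered or is hypothetical.

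**Current members.** A reader might infer that someone who still meets with a group is plainly eligible and can be made a control. The documents do not support that firmly. The compliance items (vii) ask for willingness to meet all trial requirements, and six months without Hans Kai is the control condition. The text after Fig. 2 limits invitations to people eligible to enter the program, and the wording about enrolling and joining presupposes non-members. Hans Kai staff also help judge stable health status at eligibility, so they may recognize members. This stands for current members, though it is indirect. It does not reach past ones.

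**Controls who already benefited.** A reader might also infer that a previously exposed control shrinks the contrast by already carrying the program's effect. With change from baseline as the outcome, an earlier benefit sits in the baseline score. A stable past member then behaves like any other control, and one whose benefit is fading would widen the contrast. The control-side harm is limited to continued attendance during the six months.

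**Size.** The exposed share is unknown, and no benefit at all from repeating the program is the extreme assumption. The only observed change in the protocol is +6.5 at 6 months in 34 earlier participants, without a control group. Diluted by 20% it is 6.5 × 0.8 = 5.2, and power at 60 against 30 is Φ(5.2/1.118 − 1.96), above 99%. This stands, with the caveat that an uncontrolled change is a weak guide to a between-arm difference. It is why the power losses are illustrations and not forecasts.

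**Condensed article.** The full protocol may say more about the program's own entry rules. But the article prints the trial's criteria as a complete list, so the gap is in the rule as published.

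**Conclusion.** The point holds as a minor design gap: the entry rule as printed admits people who have already been through Hans Kai. Current members are probably kept out by other text; past graduates and lapsed members are not.

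The consequence is attenuation and lost power. Randomization balances prior exposure in expectation, so a reader should not infer a bias that favors one arm, although chance imbalance is possible with only 35 controls. The harm comes from smaller further gain among exposed people in the intervention arm, from any control who keeps attending a self-run group, and from a blurred exposure-time variable in the secondary analysis.

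For a true difference of 3.1, the loss runs from about 4 percentage points of power at 5% exposed to 19 at 20%, if exposed entrants show no between-arm difference. It is about half that if they keep half the effect, and negligible if few exposed people volunteer. No stated sample-size figure is wrong.

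**What to change.** Add one exclusion criterion to the Participants section: any earlier attendance at a Hans Kai health school or membership of a Hans Kai group. Check it with one screening question and, where available, against program attendance records.

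If recruitment has already begun, record prior attendance at baseline for everyone randomized and add a sensitivity analysis of the primary outcome without those participants.

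The cost is one criterion, one question and the loss of a few otherwise eligible volunteers. The sample-size calculation does not change.

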#### Sample size

The primary analysis will be performed based on the pre- to post-intervention changes in the primary outcome, the Mental Health Continuum Short Form (MHC-SF) [23], comparing the mean change scores between the intervention and control participants, with a nested design to account for participant group membership in Hans Kai [24]. Based on data from previous studies [4, 24] and the RCT study design, we expect the changes from baseline MHC-SF scores within each subject group to be approximately normally distributed with a standard deviation of 5. The average within-group pre-post changes in MHC-SF scores in the Hans Kai prospective cohort study were + 6.5 in 34 participants at 6 months [18]. With a planned sample size that accounts for dropouts of 90 adults, with 60 intervention participants and 30 control participants, we would have a power of 80% to detect a true difference in the mean response of intervention and control participants of − 3.1 or 3.1 at the end of the 6-month RCT component [25]. This scenario assumes that the outcomes of each participant will be independent of the Hans Kai peer group they join. However, since part of the Hans Kai program includes forming groups, a very conservative power calculation considers the “effective” sample size for the Hans Kai program to be equal to the number of groups rather than the number of participants. We anticipate that 60 intervention participants will form 10 independent groups of six participants per group. In this very conservative scenario, with 10 groups in the intervention arm and 30 control participants, we would be able to detect a true difference in the mean scores of intervention and control participants of − 5.2 or 5.2 with 80% power. We believe that the actual study power will fall somewhere between the two scenarios presented here. With a starting sample size of 105 adults and an estimated 15% dropout rate during the study period [18], we expect to generate a minimum sample of approximately 90 participants at the 18-month follow-up.

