#### Outcomes

All study outcomes will be measured pre- and post-intervention at multiple timepoints and will be assessed using a multi-method approach involving subjective self-report measures and objective indicators (see Table 1 for details). The primary objective of this RCT is to measure the impact of the Hans Kai program on participant mental health using the MHC-SF [24] by comparing the MHC-SF scores obtained by the intervention group with those of the control group. The MHC-SF is a 14-item standardized self-report questionnaire that assesses emotional, social, and psychological wellbeing of respondents by investigating the regularity with which they experience symptoms of positive mental health. This scale shows high internal consistency (*α* = and moderate test–retest reliability, as well as good convergent and discriminant validity when it is used to measure mental wellbeing in Western contexts [23].

**Table 1 Tab1:** Quantitative objectives, outcome measures, and timepoints of assessment

Objectives	Outcome measures	Timepoints of assessment
*Primary objective:*		
To compare the effects of the Hans Kai program versus standard care on mental health	Mental Health Continuum Short Form (MHC-SF)	The MHC-SF will be completed at each assessment visit
*Secondary objectives:*		
1) To compare the effects of the Hans Kai program versus standard care on social connections	1) Revised UCLA Loneliness Scale	The UCLA Loneliness Scale will be administered at baseline and then every 6 months of the Hans Kai program or standard care control
2) To compare the effects of the Hans Kai program versus standard care on health-related knowledge and empowerment (i.e., self-efficacy and self-determination)	2) Perceived Health Competence Scale (PHCS)	The PHCS will be administered at baseline and then every 6 months of the Hans Kai program or standard care control
3) To compare the effects of the Hans Kai program versus standard care on health-promoting behaviors (i.e., diet, alcohol consumption, tobacco use, physical activity, and sleep)	3a) Modified version of the Healthy Eating Assessment 3b) Pittsburgh Sleep Quality Index (PSQI) 3c) Fitbit	All self-report measures will be administered at baseline and then every 6 months of the Hans Kai program or standard care control Participants will be asked to wear a Fitbit for a total of seven days at baseline and then every 6 months of the Hans Kai program or standard care control
*Tertiary objective:*		

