##### The 6-month RCT

During the 6-month RCT period, the intervention group will complete the health school (2 months) and start regular Hans Kai group meetings (6 months). During this period, the intervention group participants will complete the MHC-SF at the end of the health school and 3 months after the end of the health school, as well as all physical and mental health assessments 6 months after the end of the health school. During the 6-month RCT period, the control group will have access to standard care and will complete the MHCF-SF (3 months after enrollment) as well as all physical and mental health assessments (6 months after enrollment). In both groups, the primary outcome mental health, measured via the MHC-SF, will be assessed at baseline as well as at the 3-month and 6-month timepoints.

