#### Statistical analysis

Preliminary analysis will involve computing descriptive statistics for all quantitative variables. For continuous variables, means, standard deviations, and quartiles will be estimated, while categorical variables will be summarized with counts and percentages in each category. Summaries will be performed by group and by assessment, as well as for the entire study group. Primary data analysis of the RCT portion will involve comparing the mean values of the within-subject changes in outcome variables from baseline to 6 months between the treatment and control groups. Secondary data analysis will include a test of the interaction between time in the Hans Kai program and the outcome measurements in all participants from 0 to 20 months. The primary analysis will be conducted at the 0.05 level of significance. In general, test results will be described as significant if their *p*-values are less than 0.05 without adjustments for multiple inference. Multiple imputation will be used to deal with missing data.

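### Adding baseline MHC-SF as a covariate to the planned nested change-score analysis would gain precision at almost no cost; the gain depends on a correlation the protocol does not give

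*Protocol article*

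**What the plan says.** The protocol article describes the primary analysis in two places, and they agree. Under Sample size: "The primary analysis will be performed based on the pre- to post-intervention changes in the primary outcome", the MHC-SF, "comparing the mean change scores between the intervention and control participants", "with a nested design to account for participant group membership in Hans Kai". Under Statistical analysis, the primary analysis is "comparing the mean values of the within-subject changes in outcome variables from baseline to 6 months between the treatment and control groups". Neither section names a baseline covariate.

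The sample size rests on the change score: changes are expected to be "approximately normally distributed with a standard deviation of 5". With 60 intervention and 30 control participants, the stated detectable difference is 3.1 points at 80% power. If the 10 Hans Kai groups are counted as the units in the intervention arm, it is 5.2 points. The authors expect the actual power to lie between these two scenarios.

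Under The 6-month RCT, the MHC-SF in both arms "will be assessed at baseline as well as at the 3-month and 6-month timepoints". The Randomization and Procedure sections place the baseline assessment before allocation. The Outcomes section credits the MHC-SF with "moderate test–retest reliability". No correlation between baseline and 6-month scores is given.

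**The concern.** Comparing mean changes amounts to fixing the coefficient of baseline at 1. When baseline and follow-up are imperfectly correlated, the best-fitting coefficient is below 1, and fixing it at 1 adds noise to the arm difference. Two things are at stake.

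- **Precision.** The trial expects 90 completers, only 30 of them controls, and the protocol accepts that clustering will reduce power below the independent scenario. Precision available from data already collected is worth having.
- **Chance imbalance.** If the arms differ at baseline by luck, regression to the mean carries part of that difference into a change-score estimate. Baseline adjustment removes it under the linear model.

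**Working it through.** **Inputs from the protocol article.** SD of change 5; 60 versus 30 analysed; 80% power (Sample size). Significance level 0.05 (Statistical analysis), taken as two-sided because the difference is stated in both directions.

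**Input not in the protocol.** The correlation rho between baseline and 6-month MHC-SF. It is an assumption here, shown at 0.5, 0.7 and 0.9.

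**Step 1: reproduce the stated figures.** Detectable difference = (1.960 + 0.842) × SD × sqrt(1/n1 + 1/n2).

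- 60 versus 30: 2.802 × 5 × sqrt(1/60 + 1/30) = 2.802 × 5 × 0.2236 = 3.13. The t distribution gives 3.17. The protocol says 3.1. Power at 3.1 is 79% (normal) or 78% (t).
- 10 versus 30: 2.802 × 5 × 0.3651 = 5.11, or 5.25 with t. The protocol says 5.2.

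Both figures reproduce to within rounding and choice of approximation.

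**Step 2: the effect of baseline adjustment.** Let sigma be the SD of the score at each time, assumed equal, with the same baseline slope in both arms.

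- Variance of a change = 2 sigma² (1 − rho).
- Residual variance after adjusting for baseline = sigma² (1 − rho²).
- Ratio = (1 + rho)/2, so the SD of 5 becomes 5 × sqrt((1 + rho)/2).

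| Assumed rho | Variance ratio | Residual SD | Detectable difference, normal (t) | Power at 3.1, normal | Completers needed by change score to match 90 |
|---|---|---|---|---|---|
| Change score as planned | 1 | 5.00 | 3.13 (3.17) | 79% | 90 |
| 0.5 | 0.75 | 4.33 | 2.71 (2.74) | 89% | 90/0.75 = 120 |
| 0.7 | 0.85 | 4.61 | 2.89 (2.92) | 85% | 90/0.85 = 106 |
| 0.9 | 0.95 | 4.87 | 3.05 (3.09) | 81% | 90/0.95 = 95 |

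The t figures for adjustment allow for the one degree of freedom spent on the covariate.

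**Step 3: which rho fits the plan's own SD.** From 25 = 2 sigma² (1 − rho), sigma = 5/sqrt(2(1 − rho)). This is 5.0 at rho 0.5, 6.5 at 0.7 and 11.2 at 0.9. The protocol gives no cross-sectional SD, so it does not settle which row applies. If sigma were 10 (an assumption), rho would be 1 − 25/200 = 0.875 and the variance ratio 0.94.

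**Step 4: chance imbalance.** Given a baseline difference d between arms, the change-score estimate is shifted by (1 − rho) × d in size. The standard error of d at 60:30 is sigma × 0.2236.

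- rho 0.5: standard error 1.12; an imbalance of two standard errors shifts the estimate by 0.5 × 2.24 = 1.1 points.
- rho 0.7: standard error 1.44; shift 0.3 × 2.89 = 0.9 points.
- rho 0.9: standard error 2.50; shift 0.1 × 5.00 = 0.5 points.

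**Step 5: the conservative scenario.** If the same factor applied to 10 versus 30, the detectable difference of 5.11 would become 4.43, 4.72 or 4.99. That condition may not hold, as discussed under the objection.

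**The case against.** The strongest reply is that nothing here is misstated. The two sections agree, the SD of change suits the planned analysis, and the power figures reproduce. That stands. A reader might infer that the analysis is biased or the power claim wrong, but neither follows. The comparison is unbiased over randomisation, and the shift in step 4 is conditional on an imbalance that averages to zero.

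A second reply is that covariates may be left to the full protocol or a statistical analysis plan. Neither section rules them out, and a model for change with baseline as a covariate gives the same treatment estimate as one for the 6-month score. This stands in part. It would be wrong to call the plan a raw two-mean comparison, because nesting by group is planned. But the form of the primary comparison is fixed twice, and the trial is sized on it, so it is fair to comment on it.

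A third reply concerns size. A reader might take the rho 0.5 to 0.7 rows as the expected gain, equivalent to 106 to 120 completers. The protocol does not support that: describing test–retest reliability as moderate argues against rho near 1 but supplies no figure. Those rows also imply a cross-sectional SD of only 5.0 to 6.5, and a wider spread means a higher rho and a smaller gain.

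Two technical limits also stand. The factor applies to participant-level variance. Peer groups form after baseline, so variation arising from group experience need not shrink with individual baseline scores. And adjustment cannot be said never to lose precision: that needs a common baseline slope, which matters under 2:1 allocation.

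**Conclusion.** The point holds as a free improvement, not as an error. As written, the primary analysis leaves unused a baseline measurement that every participant provides before allocation. Under equal variances and a common slope, using it lowers participant-level variance by 25%, 15% or 5% at an assumed rho of 0.5, 0.7 or 0.9. That is worth about 10, 6 or 2 percentage points of power at a difference of 3.1. It also removes, under the linear model, a conditional shift of roughly 0.5 to 1.1 points for a two-standard-error baseline imbalance. The direction of the gain is secure under these assumptions. Its size is not, because it depends on a correlation the protocol does not give and may be smaller on the between-group component.

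**What to change.** In the Sample size and Statistical analysis sections, state that the 6-month arm difference in MHC-SF is estimated from the planned nested model with baseline MHC-SF as a covariate. The outcome may be either the 6-month score or the change, since the estimate is the same. Adjust each continuous secondary and tertiary outcome for its own baseline in the same way. Unadjusted mean changes can stay as descriptive summaries. If a separate statistical analysis plan already adjusts for baseline, align the two documents.

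The target difference is unchanged, and no visit, instrument or participant is added. The cost is one degree of freedom and the wording, which should be settled before analysis begins.
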